## Abstract

**Background:**

Proximal humerus fractures are the third most common fracture in the elderly population and are expected to increase due to the aging population. Surgical fixation with locking plate technology has increased over the last decade despite a lack of proven superiority in the literature. Three previous randomized controlled trials have not shown a difference in patient-centered outcomes when comparing non-operative treatment with open reduction and internal fixation. Low patient enrollment and other methodological concerns however limit the generalizability of these conclusions and as a result, management of these fractures remains a controversy. By comparing the functional outcomes of locked plate surgical fixation versus non-operative treatment of displaced three and four-part proximal humerus fractures in the elderly population with a large scale, prospective, multi-centered randomized controlled trial, the optimal management strategy for this common injury may be determined.

**Methods:**

We will conduct a prospective, single blind randomized controlled parallel arm trial to compare non-operative management of proximal humerus fractures with open reduction and internal fixation using locked plating technology. One-hundred and sixty patients > age 60 with acute 3- or 4- part proximal humerus fractures will be randomized to either open reduction and internal fixation with locked plating technology or non-operative management treatment arms. The primary outcome measure is the Constant Score at 24 months post-operative. Secondary outcome measures include the American Shoulder and Elbow Surgeon’s Score (ASES), EuroQol EQ-5D-5 L Health Questionnaire Score, short form PROMIS upper extremity score and IPAQ for the elderly score. Further outcome measures include assessment of the initial classification, displacement and angulation and the quality of surgical reduction via a standard computed tomography (CT) scan; rates of non-union, malunion, arthrosis, osteopenia or other complications including infection, nerve injury, intra-articular screw penetration, reoperation rates and hospital re-admission rates.

**Discussion:**

The results of this trial will provide Level 1 evidence to guide decision-making in the treatment of proximal humerus fractures in the elderly population.

**Trial registration:**

ClinicalTrials.gov NCT02362100. Registered 5 Feb 2015.

## Background

Proximal humerus fractures account for 6% of all fractures [1] and are the third most common extremity fracture in the elderly population following hip and distal radius fractures [2]. Associated with an aging population, the incidence of osteoporotic proximal humerus fractures is increasing and is expected to triple over the next three decades [3]. The majority of proximal humerus fractures are minimally displaced and can be treated non-operatively. Controversy remains regarding the optimal care of displaced fractures with potential treatment options of non-operative management, percutaneous fixation, open reduction internal fixation and arthroplasty [4–8].

### Non-operative treatment of displaced fractures

Non-operative management of proximal humerus fractures with a period of immobilization and progressive physiotherapy is a simple, noninvasive and readily available treatment option. In a systematic review of non-operative management, Iyengar et al. [9] evaluated 12 studies (*n* = 650) [10–21], with a mean age of 65.0 years and a mean follow-up of 3.8 years (range of 1–10 years). Based on the Neer classification [22], there were 49% undisplaced or one-part (*n* = 317), 25% two-part (*n* = 165), 21% three-part (*n* = 137), and 5% four-part (*n* = 31) fractures. Although variable, all treatment protocols included a period of sling immobilization followed by progressive mobilization as tolerated. The mean rate of radiographic union was 98% (range 93–100%). Various functional outcome scores were used; with 6 studies (*n* = 272) [10, 12, 14, 19–21] showing a weighted mean Constant score of 74 (range 55–81) corresponding to a “fair” outcome. Across all studies, a 13% complication rate was reported, with varus malunion being the most common (*n* = 44 or 7%). Proximal humerus avascular necrosis was found to be uncommon (*n* = 13 or 2%) [9]. In the largest included trial, Hanson et al. reported the functional outcomes of non-operative management through a prospective evaluation of 160 patients, with 124 patients having complete 1-year follow-up. Nearly half (53.1%) were undisplaced fractures. The average Constant score was 74.3 with a mean difference between the injured and contralateral shoulder of 8.2. They found an estimated median time to definitive union of 14 weeks, and a 7% risk of delayed or nonunion. Four patients went on to require surgical fixation and 5 patients underwent arthroscopic decompression, with an eventual operation rate of 5.6% [12]. With a large focus on undisplaced fractures, these studies highlight that non-operative management of proximal humerus fractures can lead to satisfactory functional outcomes with modest complication rates. In a report of non-operative management of displaced proximal humerus fractures, Yuksel et al. reported a mean Constant score of 61.3 (*n* = 18, eight 3-part and ten 4-part; mean age of 68.2 years; mean follow-up of 3.3 years), with nonunion and osteonecrosis detected in 27.8% (*n* = 5) [23].

### Surgical fixation of displaced fractures

Displaced proximal humerus fractures are commonly treated with open locking plate fixation [4–6, 8, 24–26]. A systematic review of 514 displaced proximal humerus fractures treated with locking plate fixation (12 included studies, average age of 62, average follow-up of 2.4 years) [27–38] showed an overall healing rate of 96.6%. The review included 34.0% two-part (*n* = 175), 44.7% three-part (*n* = 230), and 21.2% four-part (*n* = 109) fractures. Nine out of the 12 studies (*n* = 376) [27–29, 32, 33, 35–38] reported an average Constant score of 73.6 when evaluating functional outcome. When stratified for fracture classification, the Constant score was significantly less for 4-part fractures in comparison to the 2-part fractures (*p* = 0.02). The overall complication rate was 48.8% with a reoperation rate of 13.8%. With the exclusion of varus malunion, the complication rate remained high at 32.6% over the 12 studies analyzed [24]. Two other multicenter studies evaluated locking plate fixation for the treatment of displaced proximal humerus fractures reported similar Constant scores of 70.6 and 72 at a minimum of 1 year follow-up, and overall complication rates of 40 and 45% [25, 26]. The Proximal Fracture of the Humerus Evaluation by Randomisation (PROFHER) trial was another multi-centered randomized controlled trial of 250 patients > age 16 which showed no difference between operative and nonoperative management using the Oxford shoulder score and the Short Form 12 (SF-12). The complications in the surgical and nonsurgical group were reported as 24% and 18% respectively [39].

Despite the lack of superiority demonstrated, there has been a significant increase in surgical fixation of proximal humerus fractures following the introduction of locking plate technology over the last decade [40, 41]. Associated with high complication rates, open reduction and internal fixation of isolated proximal humerus fractures in the elderly has also been found to be an independent risk factor for inpatient adverse events and mortality [42].

Previous comparisons of non-operative and locking plate fixation have been conducted with no clear consensus as to the optimal management of osteoporotic proximal humerus fractures. No difference in the quality adjusted life years (QALYs) and societal costs between the two treatment options have been demonstrated [43]. In a randomized control trial evaluating 60 displaced 3-part proximal humerus fractures, Olerud et al. found no statistically significant difference in functional outcomes (Constant, Disability of the Arm Shoulder and Hand (DASH), and health-related quality of life (HRQoL) scores) between non-operative management and locking plate fixation over a 2-year period. One patient (3%) in the non-operative group went on to require surgical intervention and 9 patients (30%) in the locking plate group had a secondary operation with a major complication rate of 13% [44]. Fjalestad and Hole have recently reported on 50 elderly patients with displaced proximal humerus fractures randomized to non-operative or operative management using locking plate fixation. Fracture patterns were categorized based on the AO/OTA classification system, which makes a direct comparison to the study by Olerud et al. difficult. With the Constant score as their primary outcome, Fjalestad and Hole found no significant functional or HRQoL difference over a 2-year follow-up period. Similar to previous studies [25, 26], a 35% overall complication rate with surgical management was reported [45]. Both randomized control trials were limited by a small number of enrolled patients [44, 45].

It is generally accepted that non-operative management is ideal for undisplaced proximal humerus fractures, while displaced four-part fractures can be treated with non-operative management, surgical fixation or arthroplasty options [5, 6]. With no consensus in the literature, the specific management of displaced two and three-part proximal humerus fractures remains highly variable, with non-operative and locking plate surgical fixation the two most common and readily available treatment options. Given the lack of consensus on optimal treatment, conflicting, low quality-of-evidence reports, and higher level of evidence studies beset by various limitations, treatment remains highly controversial. By comparing the functional outcomes of surgical fixation versus non-operative treatment of displaced two, three and four-part proximal humerus fractures in the elderly population, the optimal management strategy for this common injury may be determined. The results of this trial would have the potential to minimize unnecessary complications and provide much needed guidance to orthopedic surgeons striving to maximize patient function and provide quality patient care in an era of rapidly increasing health care costs.

## Objectives

### Primary objective

A.Our primary objective is to determine if there is a difference in the functional outcome between non-operative management and locking plate surgical fixation of low-energy displaced three- and four-part proximal humerus fractures in the elderly population based on the Constant functional outcome score [46] over a 2-year follow-up period.

### Secondary objectives

A.Is there a difference between non-operative management and locking plate surgical fixation of low-energy displaced three- and four-part proximal humerus fractures in the elderly population based on the ASES functional outcome score [47], the short form Patient Reported Outcomes Measurement Information System (PROMIS) upper extremity score [48], the International Physical Activity Questionnaire (IPAQ) for the elderly [49], and the EuroQol EQ-5D-5 L Health Questionnaire Quality of Life (QoL) functional outcome score [50] over a 2-year follow-up period? What is the incidence of complications of non-operative management and locking plate surgical fixation of low-energy displaced three- and four-part proximal humerus fractures in the elderly population based on infection, nerve injury, intra-articular screw penetration and bleeding (hematoma), reoperation rate, or hospital readmission over a 2-year follow-up periodB.Does a difference exist between non-operative management and locking plate surgical fixation of low-energy displaced three- and four-part proximal humerus fractures in the elderly population based on radiographic outcomes including time to union, non-union, malunion, and joint arthrosis?C.Does the degree of initial displacement or angulation of the fracture fragments correlate with final functional outcome measures?D.Does the quality of the surgical reduction correlate with final functional outcome measures?

## Methods

### Study design

This study is designed as a single-centered prospective, single blind, randomized controlled trial (RCT) with parallel arms comparing nonoperative management with locked plate open reduction and internal fixation (ORIF) of proximal humerus fractures. After enrollment, patients will be randomly allocated to receive either nonoperative or operative fixation of their proximal humerus fractures. This study will abide by the current international research standards and will be reported as per the guidelines in the CONSORT statement [51]. Approval was obtained from the Health Science Network Research Ethics Board of Ottawa and is in compliance with: Ethical Conduct for Research Involving Humans; the International Conference Harmonization Good Clinical Practice: Consolidated Guideline and the provisions of the Personal Health Information Protection Act 2004. All surgical procedures will be performed by fellowship trained shoulder surgeons in a large University-affiliated hospital.

### Purpose and hypothesis

The main purpose of this trial is to determine whether or not a functional difference exists between operative and nonoperative management of low-energy displaced three- and four-part proximal humerus fractures as measured by the Constant, (PROMIS) upper extremity score, the International Physical Activity Questionnaire (IPAQ) for the elderly, and the EuroQol EQ-5D-5 L Health Questionnaire Quality of Life (QoL) functional outcome score [46, 48–50] over a period of 24 months. We will also aim to determine which method of treatment is associated with a higher incidence of complications as well as the time to union of malunion, nonunion and joint arthrosis. Lastly, we will determine whether initial displacement or quality of surgical reduction has an impact on functional outcome.

We hypothesize that there will be no statistically significant difference in functional outcomes between operative and nonoperative methods. We also hypothesize that there will be a greater incidence of complications in the operative group. Lastly, we hypothesize that fractures with a greater Neer classification and those with a greater degree of initial displacement will have worse functional outcomes.

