### Sample size calculation

The sample size will be 160 patients. The minimum clinically important difference for the Constant score is 12 [52, 53], with standard deviation of 23.1 from measurements in previous studies of similar patient populations. For the primary outcome, to achieve 80% power to detect a clinically meaningful difference of 12 points on the Constant score, with standard deviation of 23.1, and alpha of 0.05, a sample size of approximately 116 people would be necessary (58 per arm). The overall sample size is increased from 116 to 129 to account for an expected 5% crossover from the non-operative study arm to the operative study arm. An additional 31 patients were added for a conservative sample size adjustment accounting for 20% loss-to-follow-up over the two years of follow-up, for a total sample size of 160 patients.

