### Primary objective analysis

A.The analysis involves a comparison of the mean Constant scores between the two groups on an intention-to-treat basis. An ANOVA will be used to assess whether there is a statistically significant difference between treatment groups for the mean Constant scores at 2 years, with stratification factor included. A non-parametric Kruskal-Wallis will be instead used if parametric tests are not justified. In addition, a Generalized Estimated Equations (GEE) analysis will be conducted to determine whether there is an effect over time (repeated measures) (i.e. pre-operatively, 3, 6, 12 and 24 months follow-ups).

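### The functional hypothesis is the null of the planned superiority test, so a non-significant p value cannot support it; the confidence interval should be read against the protocol's own 12 points

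*Protocol article*

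**What the plan says.** Under Purpose and hypothesis the protocol article writes: "We hypothesize that there will be no statistically significant difference in functional outcomes between operative and nonoperative methods".

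The rest of the design looks for a difference:

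- Primary objective: "Our primary objective is to determine if there is a difference in the functional outcome between non-operative management and locking plate surgical fixation".
- Sample size calculation: "The minimum clinically important difference for the Constant score is 12"; the trial is sized "to achieve 80% power to detect a clinically meaningful difference of 12 points on the Constant score", taking an SD of 23.1 and a significance level of 0.05.
- Primary objective analysis: "The analysis involves a comparison of the mean Constant scores between the two groups on an intention-to-treat basis", and "An ANOVA will be used to assess whether there is a statistically significant difference between treatment groups", at 2 years. A Kruskal-Wallis test is the fallback and a GEE analysis over time is added.

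The article gives no equivalence or non-inferiority margin and no rule for reading a non-significant result from its confidence interval. The 12 points serve only as the difference to detect. Under Compliance and loss of follow-up, patients who cross over stay in their assigned group.

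**The concern.** The hypothesis is worded as the outcome of a significance test, and that outcome is failure to reject. A test built to detect a difference cannot confirm its own null. As worded, the sentence is met by any p value above the threshold, so higher variance, more loss to follow-up and more crossover all make it easier to meet.

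What is at stake is what the trial can conclude if it finds what its investigators expect. The Discussion links the question to avoiding unnecessary surgery. A non-significant result with an interval close to zero would inform that choice. One with an interval reaching well past 12 points would not. The stated hypothesis treats the two alike.

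**Working it through.** **Inputs.** Difference to detect 12, SD 23.1, alpha 0.05, power 80%, 58 per arm before inflation, 160 in total, 20% loss (Sample size calculation); final significance level 0.049 (Statistical analysis). Evaluable patients per arm: 58 (the protocol's base figure), or 160 × 0.8 / 2 = 64.

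**Step 1. Reproduce the plan's figure.** n per arm = 2 × [23.1 × (1.960 + 0.842) / 12]² ≈ 58.2, so 59 rounded up against 58 stated. Power at 58 per arm is 79.9%. A one-sided calculation would give 46 per arm. Inflation: 116 / 0.95² = 128.5, so 129; 129 / 0.8 = 161.25, against 160 stated. The figure is a two-sided superiority calculation and reproduces within two patients at each stage.

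**Step 2. Precision.** SE = 23.1 × √(2/n); half-width = 1.96 × SE. The largest non-significant estimate is just under one half-width, so its far confidence limit is just under two half-widths.

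| Evaluable per arm | SE | 95% half-width | Furthest limit with p > 0.05 | Estimate must be within this of zero to exclude 12 |
|---|---|---|---|---|
| 58 | 4.29 | 8.4 | 16.8 | 3.6 |
| 64 | 4.08 | 8.0 | 16.0 | 4.0 |
| 80 (no loss at all) | 3.65 | 7.2 | 14.3 | 4.8 |

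Using 0.049 instead of 0.05 changes the half-widths by less than 0.05 points.

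**Step 3. How often a null result would be uninformative if the true difference is zero.** The result is non-significant but its 95% interval reaches ±12 with probability 2 × [Φ(1.96) − Φ(12/SE − 1.96)].

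- 58 per arm: 12/4.29 − 1.96 = 0.84; 2 × (0.975 − 0.799) = 0.35.
- 64 per arm: 12/4.084 − 1.96 = 0.98; 2 × (0.975 − 0.836) = 0.28.

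**Step 4. How often the interval would lie inside ±12 if the true difference is zero.** Probability = 2 × Φ(12/SE − z) − 1.

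| Evaluable per arm | 95% CI (z = 1.960) | 90% CI (z = 1.645) |
|---|---|---|
| 58 | 60% | 75% |
| 64 | 67% | 80% |

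**Step 5. How often a real difference would be non-significant.** At a true 12 points: 20% with 58 per arm, 16% with 64. At a true 8 points: 54% and 50%.

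**The case against.** The strongest reply is that the design is coherent as a superiority trial. The objective, the purpose sentence, the sample size and the test all ask whether a difference exists. The criticised sentence stands beside two other predictions and can be taken as the investigators' expectation, not a decision rule. How a non-significant result is read may also be set out in an analysis plan that is not shown. Much of this stands: the sample size is right for its purpose, and the superiority test needs no change. It does not rescue the sentence, which is fixed in the protocol and is worded so that imprecision satisfies it.

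A reader might infer more than the documents support:

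- *That non-significance would be reported as proof of equivalence.* No section says so; this would be a guess about future reporting.
- *That the protocol faults the earlier trials for this same error.* It faults the two smaller ones for low enrolment and the largest for its age range, blinding, use of hemiarthroplasty, rehabilitation and low-enrolling centres. It does not fault any of them for reading a null result as equivalence.
- *That large differences would usually be missed.* At a true 12 points the miss rate is 16% to 20%. The 16 to 17 point limits belong to results just short of significance; an estimate within about 3.6 to 4.0 points of zero would exclude 12.
- *That crossover is ignored.* The sample size allows for it, and 5% one-way crossover dilutes a 12-point effect by only about 0.05 × 12 = 0.6 points. The direction is still towards the stated hypothesis.
- *That the trial can deliver formal equivalence as it stands.* The 80% in step 4 needs a 90% interval, 64 evaluable per arm and a true difference of exactly zero. At a true difference of 3 points it falls to Φ((5.28 − 3)/4.084) − Φ((−5.28 − 3)/4.084) = 69%, where 5.28 = 12 − 1.645 × 4.084. With a 95% interval, 80% power at zero difference needs 156 evaluable patients, or 156 / 0.8 = 195 randomised before any crossover allowance.

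**Conclusion.** The point holds as a mismatch between the stated hypothesis and the test that is meant to address it. A non-significant p value cannot support the hypothesis. With 58 to 64 evaluable per arm it can leave up to about 16 to 17 Constant points open, against a stated important difference of 12. If the treatments are truly equal, about 28% to 35% of such trials would be non-significant and still unable to exclude 12 points.

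These figures assume the protocol's SD of 23.1, a normal approximation and no precision gained from covariates. A smaller residual SD would narrow the intervals. The finding does not show that the sample size or the superiority test is wrong, nor that the trial must become an equivalence trial.

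**What to change.** Replace the hypothesis sentence with a two-sided null (equal mean 24-month Constant scores in the two arms) and alternative (unequal means). The investigators' expectation can be kept if it is labelled as such. Leave the superiority test and sample size unchanged, and add the following reading, fixed before outcome data are compared by arm:

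- If the primary test is significant, conclude that there is a difference and report its size with the 95% interval.
- If it is not significant and the 95% interval for the 24-month difference in means lies wholly within ±12, conclude that there is no clinically important difference.
- If it is not significant and the interval reaches beyond ±12, call the result inconclusive.

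Report the interval for the difference in means even if the Kruskal-Wallis fallback is used, since the rule depends on it. Add a supporting analysis in patients treated as allocated, because crossover under intention to treat pulls the arms together. Justify 12 points as a margin: the protocol supports it only as a difference to detect.

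The cost is one paragraph and no patients. The downside is that some non-significant results must be called inconclusive. With a 95% interval, the chance of landing inside ±12 is only about 60% to 67% even when the true difference is zero (75% to 80% with a 90% interval), so the trial should not be described as powered for equivalence.
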